### Sample size/power calculation

Accepting an alpha risk of 0.05 and a beta risk of less than 0.2 in a bilateral contrast, 200 subjects will be necessary in each group, in order to detect a statistically significant difference which in the control group is expected to be 0.5 and in the intervention group 0.65. A loss-to-follow-up rate of 5% is estimated. The ARCSINUS approximation (GRANMO Sample Size Calculator v.7.12 available at www.imim.es) was used.

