#### Randomization

All participants included in the study will be assigned to the control or intervention group (IG) in a 1:1 ratio using the EPIDAT programme (General Directorate of Innovation and Public Health Management, Xunta de Galicia, Spain; version 3.1). The randomisation will be carried out by the primary care centre and centralised from the Research Support Unit of IDIAP Jordi Gol of Tarragona with a simple numerical randomisation ratio.

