#### Statistical analysis

The efficacy of randomisation will be tested by assessing the comparability and homogeneity of the groups in terms of the similarity of the distribution of the variables of interest at baseline. In addition, the proportion of losses in each group during follow-up will be quantified and assessed as to whether these are independent of the study intervention.

Analysis will be performed as intention to treat. To assess the theoretical bias due to loss to follow-up will be assessed using the 'worst-case analysis' strategy, which will assume that lost patients (in both groups) continue smoking. In case of reporting abstinence but not presenting at the final follow-up visit, self-reported but unconfirmed abstinence will be considered.

Standard statistical tests will be used to analyse the described continuous and categorical variables (e.g. mean, standard deviation, proportions, etc.). Continuous variables will be compared using the Student’s t-test when following a normal distribution or using the U-Man Whitney test if variables are not normally distributed. For categorical variables, Pearson's chi-square test will be used. Point abstinence rates at the end of pregnancy and prolonged abstinence, 12 months after the intervention, will be compared between both groups.

To assess the effectiveness of implementation, odds ratios of association between the allocation group and prolonged abstinence will be calculated. Odds ratios will be calculated crude and adjusted for clinically relevant covariates and relevant interactions between them. Survival analysis will also be carried out for prolonged abstinence at 12 months from counselling smoking cessation. A multivariate Cox regression analysis will be performed comparing the two groups using the Log-Rank test to calculate the Hazard Ratio for abstinence at the end of pregnancy and prolonged abstinence at 12 months after the intervention.

The relationship between missing data and the main variables will be analysed. If missing values exceed 3%, the possibility of applying missing imputation techniques will be studied.

All statistical analysis tests will be conducted with R Statistics package (R foundation for statistical computing, Vienna, Austria; version 4.1.2 or later) and will be considered significant when *p* < 0.05.

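### The stated sample-size inputs give about 179 per group, not 200; the 5% loss rate and the 200 do not reproduce each other, although 200 meets the power target at 5% loss

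*Protocol article*

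**What the plan says.** The section on sample size and power gives a full set of inputs:

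- Error rates: "Accepting an alpha risk of 0.05 and a beta risk of less than 0.2 in a bilateral contrast".
- Abstinence: the proportion "in the control group is expected to be 0.5 and in the intervention group 0.65".
- Method: "The ARCSINUS approximation (GRANMO Sample Size Calculator v.7.12".
- Loss: "A loss-to-follow-up rate of 5% is estimated".
- Result: "200 subjects will be necessary in each group". The Methods part of the abstract repeats 200 per group.

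The Randomization section fixes equal allocation, "in a 1:1 ratio using the EPIDAT programme". The Statistical analysis section plans an intention-to-treat analysis. To address bias from loss it adds a worst-case strategy, "which will assume that lost patients (in both groups) continue smoking".

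**The concern.** The article states inputs, method and result together, so a reader should be able to get from one to the other. This is not detail that could be waiting in a separate analysis plan: the figures are all on the page and they disagree. Either an input differs from what was used, or an unstated assumption or rounding step lies behind the 200.

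The loss rate deserves care for a second reason. Dividing by one minus the loss rate preserves power only if lost women drop out of the comparison. If they stay in as smokers, both abstinence proportions shrink and so does their difference, and the allowance does not fully restore the power. How much loss the design can absorb therefore depends on which loss rate was really used and which rule governs the main comparison.

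**Working it through.** **Inputs.** From the sample-size section: alpha 0.05 two-sided (z = 1.960), power 80% (z = 0.8416), p1 = 0.50, p2 = 0.65, loss 5%, arcsine method. From the Randomization section: 1:1 allocation.

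**Step 1: the plan's own calculation.**

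- h = 2·asin(√0.65) − 2·asin(√0.50) = 0.3047
- n = 2·(1.960 + 0.8416)² / h² = 169.1, so 170 per group before loss
- With 5% loss: 170/0.95 = 178.9, so 179 per group, or 358 in total against the planned 400. Multiplying instead, 170 × 1.05 = 178.5, gives the same 179; dividing the unrounded 169.09 by 0.95 gives 178.

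The excess is 200 − 179 = 21 per group, or 42 women; 200/179 = 1.12.

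**Step 2: does another standard formula explain 200?** Keeping alpha, power and the 5% loss as stated:

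- pooled normal formula: 170 before loss, 179 after
- unpooled normal formula: 176 after loss
- continuity-corrected (pooled or arcsine): 183/0.95, so 193
- sized on rates already reduced by 5% (0.475 against 0.6175): 191

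None gives 200 without further rounding up.

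**Step 3: which unstated inputs come near 200?**

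- 15% loss: 170/0.85 = 200.0 (unrounded, 169.09/0.85 = 198.9, so 199)
- 10% loss with continuity correction: 204
- 85% power: 194 with no loss, 204 to 205 with 5% loss
- one-sided test at 90% power with 5% loss: 195

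**Step 4: power at 200 per group.** Power = Φ(h·√(n/2) − 1.960). With lost women excluded, n becomes 200(1 − L). With lost women counted as smoking, n stays 200 and the rates become 0.50(1 − L) and 0.65(1 − L).

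| Loss L | Rates, lost = smoking | Power, lost = smoking | Power, lost excluded |
|---|---|---|---|
| 0% | 0.500 v 0.650 | 86.1% | 86.1% |
| 5% | 0.475 v 0.6175 | 81.9% | 84.4% |
| 10% | 0.450 v 0.585 | 77.3% | 82.4% |
| 15% | 0.425 v 0.5525 | 72.5% | 80.2% |

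Exact enumeration of the chi-square test agrees closely for the lost-equals-smoking column (85.9%, 82.0%, 77.6%, 72.8%). Power under that rule crosses 80% at a loss of about 7%. At 15% loss it would take about 240 per group to reach 80%.

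**The case against.** The strongest reply is that nothing harmful follows from the mismatch. The text asks for "a beta risk of less than 0.2 in a bilateral contrast", an inequality, and 200 per group satisfies it at the stated loss whichever way lost women are handled. A planner who arrived at 191 or 193 could well have rounded up to 200. This stands: the discrepancy is on the safe side. It does not rescue the wording, because a number described as necessary should follow from the inputs beside it, and no rounding or margin is mentioned.

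A reader might infer that the real allowance was 15%, since 170/0.85 is exactly 200. The documents do not support that as a fact. The protocol contains no 15%, the exactness depends on rounding 169.1 up to 170 first, and several other unstated inputs land close by.

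A reader might also infer that the trial is underpowered at about 72%. That figure belongs to the inferred 15% loss, not to the plan as written. It also rests on conditions that the protocol does not settle:

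- Loss is equal in both arms.
- 0.50 and 0.65 are rates among women followed up. If they already count lost women as smokers, reducing them again double-counts and power at 200 is about 86%.
- The lost-equals-smoking rule is the main comparison. The Statistical analysis section introduces it to gauge bias from loss, accepts unconfirmed self-report from women who miss the final visit, and leaves imputation open above 3% missing.

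Finally, it would be going too far to say that retention is being monitored against a wrong limit. The preliminary exploration at 10% of recruitment looks at retention, but no section sets a limit.

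**Conclusion.** The stated inputs give 170 per group before loss and about 179 after 5% loss, so the 5% and the 200 do not reproduce each other. This part rests only on the protocol's own figures and is firm. What produced the 200 cannot be determined from the text.

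On the loss rate as written, the trial has about 21 women per group more than the formula requires and meets its power target, even with lost women counted as smoking. This is an error of reporting in a figure the trial relies on, with no demonstrated effect on validity.

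The reserve is limited, however. Under the lost-equals-smoking rule, and on the first two conditions listed above, 80% power needs loss to stay at or below about 7%. The margin is worth stating because the follow-up section defines loss broadly, including one missed visit without telephone contact and transfer to another unit. If the allowance actually used was 15%, the stated beta would not be met under that rule.

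**What to change.** Keep 200 per group and rewrite the paragraph so that it reproduces:

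1. State the loss rate and power actually used. If 5% and 80% are right, wording such as the following would do: *170 per group are needed before loss and 179 allowing for 5% loss; 200 per group will be enrolled.*
2. Say whether 0.50 and 0.65 are rates among women followed up or rates with lost women already counted as smoking.
3. Report power at 200 per group under the lost-equals-smoking rule: about 82% at 5% loss, 77% at 10% and 72% at 15%, falling below 80% beyond about 7%. Label these as assuming equal loss in both arms and rates among women followed up.
4. If the sample-size records show that 15% was used, correct the 5% and restate the power under that rule.

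At 5% loss the cost is a text change, with no extra participants. If 15% was the true allowance, the stated power becomes less favourable; holding 80% under the lost-equals-smoking rule would take about 240 per group, so the choice would be between a lower stated power and a larger trial.

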### Blinding

Given the nature of the intervention, it is not possible to mask the participants neither the ASSIR professionals to the study group assignments. The data will be masked for the research team carrying out the statistical analyses.

### Strategy of analysis

#### Preliminary exploration

At the recruitment point of 10% of the total sample, a first data extraction will be carried out to analyze test key elements of the trial, including recruitment and retention strategies, intervention delivery, data collection methods and adherence to the study protocol.

#### Statistical analysis

The efficacy of randomisation will be tested by assessing the comparability and homogeneity of the groups in terms of the similarity of the distribution of the variables of interest at baseline. In addition, the proportion of losses in each group during follow-up will be quantified and assessed as to whether these are independent of the study intervention.

Analysis will be performed as intention to treat. To assess the theoretical bias due to loss to follow-up will be assessed using the 'worst-case analysis' strategy, which will assume that lost patients (in both groups) continue smoking. In case of reporting abstinence but not presenting at the final follow-up visit, self-reported but unconfirmed abstinence will be considered.

Standard statistical tests will be used to analyse the described continuous and categorical variables (e.g. mean, standard deviation, proportions, etc.). Continuous variables will be compared using the Student’s t-test when following a normal distribution or using the U-Man Whitney test if variables are not normally distributed. For categorical variables, Pearson's chi-square test will be used. Point abstinence rates at the end of pregnancy and prolonged abstinence, 12 months after the intervention, will be compared between both groups.

To assess the effectiveness of implementation, odds ratios of association between the allocation group and prolonged abstinence will be calculated. Odds ratios will be calculated crude and adjusted for clinically relevant covariates and relevant interactions between them. Survival analysis will also be carried out for prolonged abstinence at 12 months from counselling smoking cessation. A multivariate Cox regression analysis will be performed comparing the two groups using the Log-Rank test to calculate the Hazard Ratio for abstinence at the end of pregnancy and prolonged abstinence at 12 months after the intervention.

The relationship between missing data and the main variables will be analysed. If missing values exceed 3%, the possibility of applying missing imputation techniques will be studied.

All statistical analysis tests will be conducted with R Statistics package (R foundation for statistical computing, Vienna, Austria; version 4.1.2 or later) and will be considered significant when *p* < 0.05.

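### The worst-case analysis for losses scores lost women as smokers in both arms, so it does not bound the App effect and can certify a robustness that was never tested

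*Protocol article*

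**What the plan says.** All of this is in the protocol article; no separate analysis plan is at hand.

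- **Statistical analysis, losses.** The analysis is by intention to treat. Bias from loss to follow-up is to be assessed with a strategy labelled worst-case, "which will assume that lost patients (in both groups) continue smoking". No other rule for lost women is given. The paragraph before it says that losses will be counted in each arm and checked for independence from the intervention. Women who report abstinence but miss the final visit are handled separately, through their unconfirmed self-report.
- **Statistical analysis, missing values.** A later paragraph says: "If missing values exceed 3%, the possibility of applying missing imputation techniques will be studied". It names no variable and does not say how it ranks against the rule for lost women.
- **Sample size/power calculation.** "200 subjects will be necessary in each group"; the proportion "in the control group is expected to be 0.5 and in the intervention group 0.65"; "A loss-to-follow-up rate of 5% is estimated".
- **Blinding.** Neither participants nor the treating professionals can be masked; the team doing the statistical analyses is masked.
- **Follow-up and data collection.** Loss covers withdrawal, a missed visit with failed telephone contact, and transfer of care to a high-risk unit or another centre.

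**The concern.** A worst-case analysis should show how far the losses could move the result against the conclusion being drawn. Here that conclusion would be that the App works. The least favourable allocation therefore counts lost App women as smokers and lost controls as abstinent. Scoring lost women as smokers in both arms lowers both rates together. With equal losses it only shrinks the difference slightly. With more losses among controls it enlarges the difference.

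Controls receive usual care and know that they were not given the App, so higher loss among them is possible. Loss also includes transfer to another unit, which says nothing about smoking. At stake is a published statement that the result survived a worst-case analysis when no such analysis was run.

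**Working it through.** **Inputs.** From the sample size section: 200 per arm, abstinence 0.50 (control) and 0.65 (App), 5% loss, which is 10 women per arm. I assume that the two rates apply to women who are followed; the article does not say so, and the other reading is given below.

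The figure of 200 is taken as stated. The arcsine formula gives (1.960 + 0.842)² / (2 × (0.9377 − 0.7854)²) = 169.1, so 170 per group, and 170/0.95 = 179 with 5% loss. The stated 200 is therefore not reproduced, but it exceeds the requirement and does not affect this point.

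**Algebra.** Let p_A and p_C be the rates among women followed, and l_A and l_C the fractions lost.

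- Plan's rule: RD = p_A(1 − l_A) − p_C(1 − l_C).
- Least favourable to the App: the plan's RD − l_C.
- Most favourable to the App: the plan's RD + l_A.

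The plan's rule therefore lies inside the range of possible results, not at its lower end.

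**Planned 5% loss per arm.**

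- Plan's rule: control 95/200 = 0.475, App 123.5/200 = 0.6175, RD 0.1425. Wald SE = √(0.475×0.525/200 + 0.6175×0.3825/200) = 0.0493. 95% CI 0.046 to 0.239; pooled z-test p = 0.004.
- Least favourable: control 105/200 = 0.525, App 0.6175, RD 0.0925, SE 0.0493. 95% CI −0.004 to 0.189; p = 0.062.
- Most favourable: 0.475 against 0.6675, RD 0.1925, p = 0.0001.

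**How extreme is the lower end?** Keep all 10 lost App women as smokers and vary the number of lost controls counted as abstinent. With 9 of 10, control is 104/200 = 0.52, RD 0.0975, z = 0.0975/0.0495 = 1.97, p = 0.049. At 5% loss only the extreme corner crosses 0.05.

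**Assumed 10% loss per arm.** Plan's rule: 0.45 against 0.585, RD 0.135 (0.038 to 0.232), p = 0.007. Least favourable: 0.55 against 0.585, RD 0.035 (−0.062 to 0.132), p = 0.48. With all 20 lost App women smoking, 8 of 20 lost controls abstinent is enough: 98/200 = 0.49, RD 0.095, z = 1.91, p = 0.057.

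**Other reading of the planned rates.** If 0.50 and 0.65 already count lost women as smokers, the plan's rule gives RD 0.150 and the least favourable case 0.55 against 0.65. That is RD 0.100, SE √(0.55×0.45/200 + 0.65×0.35/200) = 0.0487, 95% CI 0.004 to 0.196. The gap between the two is still 5 points, but the lower case stays just above zero.

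**Unequal loss with no true effect (an illustration; the loss rates are assumed).** Abstinence is 50% in both arms, with 15% of controls and 5% of App women lost at random. The rule gives control 0.50×0.85 = 0.425 and App 0.50×0.95 = 0.475, a spurious +0.05. Null SE = √(0.45×0.55×2/200) = 0.04975; SE under these rates = 0.04969. The chance of p<0.05 in the App's favour is P(Z > (1.96×0.04975 − 0.05)/0.04969) = P(Z > 0.956) = 0.169. The other tail adds 0.001, so about 17% in all against a nominal 5%.

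**The case against.** The case on the other side is substantial.

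- **The rule itself is workable.** Its assumption is written in the same sentence as its label, and at equal losses it moves the difference from 15 to 14.25 points, against the App. This stands: the fault is the label and the use as a bias check, not the rule.
- **The plan has another check.** A reader might infer that the plan cannot show bias from losses at all. That is not supported, because losses are compared between arms. But such a check detects imbalance only; it gives no estimate of what the imbalance does to the result.
- **The lower bound is extreme.** It needs every lost control to be abstinent, although the plan expects 50% in controls and the Background reports high postpartum relapse. This stands, and the bound should be read as an outer limit. Telephone contact and the self-report rule should also reduce the number of women scored by default.
- **Unequal loss is speculative.** The article gives no loss by arm. Heavier loss in the App arm would bias against the App.
- **The 3% sentence.** A reader might infer two conflicting rules for the same data, chosen after the results are seen. The text does not establish this. The sentence commits only to studying imputation and may concern covariates or secondary variables. If every lost woman is coded as smoking, her loss leaves no missing primary outcome. Missing values and loss to follow-up are also different quantities, and the analysts are masked. What remains is that scope and precedence are unstated, while the planned 5% loss would pass a 3% threshold if it were counted.
- **Detail may sit in an analysis plan not shown.** That covers missing detail, but not a check that the article defines and labels wrongly.

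**Conclusion.** The concern holds in a limited form. The analysis offered as the assessment of bias from losses is a single symmetric assumption that does not bound the App effect. At the planned 5% loss per arm it lies 5 points above the least favourable case: 14.3 against 9.3 points, with the interval of the latter reaching just below zero. At an assumed 10% loss the gap is 10 points (13.5 against 3.5).

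These figures rest on 50% and 65% applying to women followed and on equal losses. Whether the lower case excludes zero at 5% loss depends on the first assumption; the size of the gap does not. The 17% false-positive figure rests on assumed losses of 15% and 5% and shows only the direction and possible size of the problem. The documents do not show that the rule will favour the App in this trial, nor that the 3% sentence contradicts it.

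**What to change.** 1. State lost = smoking in both arms as the primary handling rule for the smoking outcome, and stop calling it a worst case.
2. Make the bias assessment the opposite-direction scenario (lost App women smoking, lost controls abstinent), with a tipping-point grid between the extremes. Report it whatever the percentage lost, beside the comparison of losses by arm that is already planned.
3. Add one sentence saying that the 3% imputation provision does not change the primary handling of the smoking outcome.

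The cost is a few sentences and a few extra analysis runs, with no new data. The robustness statement may turn out less favourable than the present rule would allow.

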## Methods

### Study objectives

The primary objective of this research is to evaluate the effectiveness of an intervention against tobacco in pregnant smokers based on the Tobbstop App, which has already been validated for smoking cessation in the general population [19, 20].

The specific objectives which have set out are:To determine the effectiveness of the intervention on smoking cessation during pregnancy.To evaluate the effectiveness of the intervention on prolonged abstinence.To analyse the impact of the intervention to reduce daily consumption in pregnant smokers who continue smoking.To determine the impact of the intervention on pregnancy, birth and neonatal health indicators.

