**Basic physical examination: **		
Weight	Kg	Basal and follow-up
Height	cm	Basal
Blood pressure	mmHg	Basal and follow-up

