**Smoking habit**		
Nicotine dependence level	Fagerström test: Low ≤ 3; Medium 4-6; High ≥7	Basal
Motivation	Richmond test: Low ≤ 4; Medium 5-6; High ≥ 6	Basal
Stage of change	Prochaska and DiClemente model : Pre-contemplation; Contemplation; Preparation; Action; Maintenance; Relapse	Basal
Consumption before pregnancy	Cigarettes/day	Basal
Current consumption	Cigarettes/day	Basal and follow-up
Type of tobacco consumption	Cigarettes; Cigars; E-Cigarettes; Smokeless Tobacco; Hookah; Pipes; Others	Basal
Age at starting smoking	Years old	Basal
Previous quit attempts	Number	Basal
Reasons for relapse	Weight gain; Stress; Nicotine withdrawal symptoms; Others	Basal
Use of drug therapy or other methods for smoking cessation during the study	Nicotine replacement therapy; Bupropion; Varenicycline; Others	Basal and follow-up
Smokers in the family	Yes; No	Basal

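### Daily consumption (Objective 3) is recorded at the basal visit and in follow-up, but the stated two-sample test does not adjust for the basal value, which would cheaply gain precision

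*Protocol article*

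**What the plan says.** The third specific objective in Study objectives reads "To analyse the impact of the intervention to reduce daily consumption in pregnant smokers who continue smoking". Table 2, under Smoking habit, has the measure for it: "Current consumption Cigarettes/day Basal and follow-up".

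Statistical analysis gives one general sentence on continuous variables. They are compared by Student's t-test "when following a normal distribution or using the U-Man Whitney test if variables are not normally distributed". The sentence names no outcome and no time point, and does not say whether the follow-up value or the change is tested.

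Elsewhere in the same section, covariates enter the odds ratios for prolonged abstinence, and a multivariate Cox model is planned for abstinence. Baseline values are mentioned only for checking that the groups are comparable. No regression model is stated for any continuous outcome.

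Table 2 also lists "Weight Kg Basal and follow-up" and "Blood pressure mmHg Basal and follow-up" under Basic physical examination. The only objective that could reach them is "To determine the impact of the intervention on pregnancy, birth and neonatal health indicators".

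**The concern.** Objective 3 asks about a reduction, so each woman's starting level matters. Basal consumption is probably the best available predictor of follow-up consumption. The inclusion criteria admit both sporadic and daily smokers, from as little as one cigarette in the last 30 days, so the spread at entry is likely to be wide. In a two-sample test on follow-up values all of that spread goes into the error term. Randomisation is described as simple 1:1 with no stratification by consumption, so the estimate also carries any chance difference in basal consumption.

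At stake is precision on a specific objective that will be studied in a reduced sample, since only women still smoking contribute. A real reduction would be easier to miss than it need be, although the data to avoid this are already collected.

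**Working it through.** **Inputs.** From the protocol (Sample size/power calculation): two-sided alpha 0.05, beta below 0.2, 200 per group, 5% loss, proportions 0.50 and 0.65 (taken here as abstinence). The 200 per group is sized on those proportions. No power or detectable difference is stated for consumption, so there is no figure of the plan's own to reproduce. The correlation ρ between basal and follow-up consumption is not given. It is an assumption, shown over a range.

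**1. Variance relative to the follow-up value alone** (equal variances at both times):

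- follow-up value only: 1
- change score: 2(1 − ρ)
- baseline-adjusted (ANCOVA): 1 − ρ²

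The change score exceeds ANCOVA by 2(1 − ρ) − (1 − ρ²) = (1 − ρ)², which is positive at every ρ below 1.

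| ρ | ANCOVA | Change |
|---|---|---|
| 0.3 | 0.91 | 1.40 |
| 0.5 | 0.75 | 1.00 |
| 0.7 | 0.51 | 0.60 |
| 0.8 | 0.36 | 0.40 |

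Change is worse than the follow-up value alone below ρ = 0.5, equal at 0.5 and better above it. ANCOVA is at least as good as either throughout.

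**2. Power under normality.** Set the difference so that the unadjusted t-test has 80% power, then replace the SD by SD × √(1 − ρ²). Power becomes 83.6% at ρ = 0.3, 89.9% at 0.5 and 97.5% at 0.7. These values do not depend on the group sizes. At ρ = 0.5 the variance falls by 25%, equivalent to 1/0.75 = 1.33 times as many women.

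**3. Size of the Objective 3 comparison.** With 5% loss, 200 × 0.95 = 190 per arm. Continuing smokers would number 190 × 0.50 = 95 in control and 190 × 0.35 = 66.5 in intervention. The difference detectable with 80% power is (1.96 + 0.84) × √(1/95 + 1/66.5) = 0.448 SD unadjusted. With adjustment it is 0.448 × √0.75 = 0.388 SD at ρ = 0.5, and 0.448 × √0.51 = 0.320 SD at ρ = 0.7.

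**4. Skewed counts.** Cigarettes per day are unlikely to be normal, and the plan would then use Mann-Whitney, so step 2 is not the whole comparison. Simulation with illustrative inputs (log-normal counts rounded to whole cigarettes, ρ = 0.5, 190 per arm) gave these approximate powers:

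| Log-SD | Mann-Whitney (planned) | Raw-scale ANCOVA, robust SE |
|---|---|---|
| 0.6 | 77% | 81% |
| 0.8 | 77% | 74% |
| 1.0 | 78% | 66% |

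ANCOVA on the log or rank scale gave about 86–89%. The gain over the planned test is therefore real on those scales, while raw-scale adjustment falls below Mann-Whitney at the two larger spreads.

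**The case against.** **The text does not say that the basal value is ignored.** A reader might infer this as fact. But the sentence on continuous variables is generic, and an objective worded as reducing consumption fits a test on change, which does use the basal value. This stands: what can be said is that no use of it in the comparison is stated. It does not remove the point, because change is less efficient than adjustment at every ρ below 1. Nor is it right to call change no better than the raw follow-up value: above ρ = 0.5 it is better.

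**Weight and blood pressure.** It is tempting to extend the point to them. Outcomes assessment lists only abstinence, and Table 2 places both under physical examination, apart from the pregnancy, birth and newborn groups. They matter here only if they are analysed as pregnancy indicators under Objective 4.

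**The planned tests are valid.** They keep their type I error, which already allows for chance imbalance. True. The loss is in precision, not validity.

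**An unseen analysis plan may specify a model.** Possibly. But the protocol does state a method for continuous variables and does describe adjustment where it intends it, for abstinence. The point concerns that stated choice.

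**Conclusion.** The point holds for cigarettes per day, as a suggested improvement to a secondary analysis (a change to consider). The stated test makes no declared use of a basal value that is already collected. At an assumed ρ of 0.5 the gain is about 10 percentage points of power: 80% to 90% under normality, or about 77% to 86–89% against Mann-Whitney with illustrative log-normal counts. Under normality it is under 4 points at ρ = 0.3 and about 17 points at 0.7. All of these rest on assumed correlations and distributions, none of which the protocol gives.

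Two stronger conclusions are not supported. The primary result is not weakened: prolonged abstinence is a separate analysis with its own adjusted odds ratio. And baseline adjustment does not make the comparison among continuing smokers a fully randomised one. That group is defined after allocation, and the selection remains whichever test is used.

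**What to change.** In Statistical analysis, replace the two-sample test for cigarettes per day with a comparison of follow-up consumption by allocation, with "Current consumption" at the basal visit (not consumption before pregnancy) as covariate:

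- Among continuing smokers: ANCOVA on the log scale, reported as an adjusted ratio of geometric means with 95% CI.
- Where women with zero consumption are included: rank ANCOVA.
- Not raw-scale ANCOVA.
- Mann-Whitney kept as a check.

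State how sporadic smokers are recorded before logs are taken. One cigarette in 30 days is 1/30 ≈ 0.03 per day, which becomes zero if rounded.

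Apply the same adjustment to weight and blood pressure only if they are to be analysed under Objective 4.

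The cost is a sentence or two of wording and a short regression in R, with no new data or visits. The small downside is that a ratio or rank effect is slightly harder to explain than a difference in cigarettes per day.
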